### Measurements

The endpoint assessors are responsible for post-intervention follow-up. They conduct regular data collection and follow-up for all participants according to the study protocol schedule. Follow-up time points are at the end of the treatment period (3 months after enrollment) and 3 months after treatment completion (6 months after enrollment). The primary endpoint is evaluated based on 24 h Holter monitoring, assessing the absence of atrial arrhythmias in both groups at the end of treatment. In this study, the occurrence of atrial arrhythmias is defined as either a single episode of AF lasting ≥30 s, or ≥100 PAVs per 24 h on Holter monitoring (21). Holter data will be collected uniformly using a single-channel ambulatory electrocardiogram recorder (model: EPBB-PAH-1A; manufacturer: Shanghai Yuanxin Medical Technology Co., Ltd.; registration no.: 20212070427). At baseline and each follow-up visit, cardiac function will be assessed via echocardiography, as well as serum levels of cTnI and NT-proBNP. Patients' quality of life will be evaluated using the FACT-G scale, ECOG performance status, clinical symptom score, and the Self-Rating Anxiety Scale (SAS). Additionally, complications, adverse events, and laboratory parameters—including complete blood count, liver and kidney function, and electrolytes—will be recorded. All baseline data will be documented by the clinical investigators responsible for participant recruitment and intervention administration.

### Outcome evaluation

#### Primary outcome

The primary endpoint is the proportion of patients in both groups free of atrial arrhythmias 3 months after intervention, defined as the absence of any single episode of AF lasting ≥30 s or PAVs ≥100 beats per 24 h as detected by 24 h Holter monitoring.

#### Secondary outcome

Secondary outcomes include: (1) AF burden (defined as the cumulative duration of all AF episodes recorded on 24 h Holter monitoring) or the frequency of PAVs on Holter monitoring at 3 and 6 months after enrollment (21). (2) Echocardiographic parameters (LVEF, LVEDD, LVESD, LAD, RVD, E/A ratio) and levels of cTnI and NT-proBNP at 3 and 6 months. (3) Other secondary measures assessed at 3 and 6 months: the FACT-G questionnaire, ECOG performance status, clinical symptom scores, and the SAS scores.

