#### Inclusion criteria

The inclusion criteria for this study include the following conditions: 1) Age 18–80 years; 2) Having a confirmed pathological type, receiving chemotherapy for the first time, with an expected cumulative anthracycline dose ≥200 mg/m², and PAVs or AF after at least one cycle of anthracycline therapy, with ambulatory electrocardiography showing PAVs ≥100 beats per 24 h or meeting the diagnostic criteria for AF; 3) No history of PAVs or AF; 4) No prior history of chest radiotherapy, targeted therapy, or immunotherapy; 5) Eastern Cooperative Oncology Group (ECOG) performance status < 2; 6) Willing to be randomly assigned to either the WXKL group or the control group; 7) Voluntary participation in the trial and provision of signed informed consent.

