### Statistical analysis

All statistical analyses will be performed using SPSS (version 26.0, IBM) and R (version 4.1.1). All tests will be two-sided, and a *P* value <0.05 will be considered statistically significant. The primary analysis will follow the intention-to-treat (ITT) principle, including all randomized participants and analyzing them according to their assigned groups. A per-protocol (PP) analysis will be conducted as a sensitivity analysis, and the safety analysis will include all participants who received at least one intervention. Baseline characteristics will be described by group. Continuous variables will be presented as mean ± standard deviation or median (interquartile range), depending on their distribution, while categorical variables will be expressed as frequencies and percentages. All analyses will be reported in accordance with the CONSORT Statement.

The primary outcome is the proportion of patients free from atrial arrhythmias at 3 months after intervention, which is a binary variable. It will be analyzed using a generalized linear model (GLM) with a binomial distribution and a log link function. Treatment group and study center will be included as fixed effects, and pre-specified baseline covariates—including age, sex, cancer subtype, cumulative anthracycline dose, and medical history—will be further adjusted. Results will be presented as risk ratios (RR) with corresponding 95% confidence intervals. Secondary continuous outcomes, such as AF burden, premature PAVs counts, echocardiographic parameters, and relevant biomarkers, will be analyzed using linear models (LM), with adjustment for baseline values. For repeated measures data (e.g., baseline, 3 months, and 6 months), mixed-effects models will be applied to evaluate treatment effects over time.

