The incidence of adverse events and serious adverse events will be summarized as frequencies and percentages, and compared between groups using the chi-square test or Fisher's exact test, as appropriate. Changes in laboratory parameters will be described descriptively and compared between groups when necessary. Pre-specified subgroup analyses will be conducted based on cumulative anthracycline dose (e.g., high vs. low dose). Interaction terms between treatment and subgroup will be included in the model, and the Wald test will be used to assess differences in treatment effects across subgroups. The normality of model residuals will be evaluated using Q–Q plots. If the normality assumption is violated, appropriate data transformations or robust statistical methods will be applied. Missing data will be handled using multiple imputation under the assumption of missing at random, and sensitivity analyses will be performed to assess the robustness of the results. No interim analysis is planned for this study.

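### PAC count is modelled on its own although it falls when a patient moves into AF; AF burden and E/A ratio also need rules suited to a population that mixes PACs and AF (secondary outcomes only)

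*Protocol article*

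**What the plan says.** All references are to the protocol article.

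- **Inclusion criteria.** Two kinds of patient qualify, those with "ambulatory electrocardiography showing PAVs ≥100 beats per 24 h or meeting the diagnostic criteria for AF".
- **Secondary outcome.** AF burden is "defined as the cumulative duration of all AF episodes recorded on" the 24 h Holter, an absolute time. The same item continues "or the frequency of PAVs on Holter monitoring at 3 and 6 months after enrollment". The next item lists "Echocardiographic parameters (LVEF, LVEDD, LVESD, LAD, RVD, E/A ratio").
- **Abstract (Methods).** PAC count and AF burden appear as separate secondary outcomes.
- **Statistical analysis.** "Secondary continuous outcomes, such as AF burden, premature PAVs counts, echocardiographic parameters, and relevant biomarkers, will be analyzed using linear models (LM"), adjusted for the baseline value. Mixed-effects models are used for repeated measures. As a fallback, "If the normality assumption is violated, appropriate data transformations or robust statistical methods will be applied". Missing data are multiply imputed under a missing-at-random assumption.
- **Primary outcome.** A patient is free of atrial arrhythmia only with neither an AF episode of at least 30 s nor 100 or more PACs per 24 h.

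**The concern.** The Introduction describes PACs as a precursor of AF and the two as stages of one process, so some patients can be expected to move between them. A premature atrial beat can be recognised only against an organised atrial rhythm, so time in AF contributes no PACs. A PAC count analysed alone therefore moves the wrong way when the disease moves along the path the article describes: worsening into AF lowers it and recovery of sinus rhythm raises it. The baseline count used as covariate has the same defect in patients who enter in AF. If the arms differ in AF at follow-up, the PAC comparison can favour the arm with more AF.

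Two related outcomes need attention for the same reason. AF burden is exactly zero in every patient without AF, and a mean difference from a linear model describes such a distribution badly. E/A needs an A wave, which AF abolishes. It will be absent because of the arrhythmia under study, and the only missing-data rule in the article, applied as written, would fill in a quantity that does not exist.

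**Working it through.** **1. The plan's own figure.** The article gives no figure for these secondary outcomes. Its sample size uses 29% versus 10%, two-sided 0.05, 80% power. With the pooled normal approximation and a mean proportion of 0.195:

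n = [1.960 × √(2 × 0.195 × 0.805) + 0.842 × √(0.29 × 0.71 + 0.10 × 0.90)]² / 0.19² ≈ 67.1, rounded up to 68 per group. Then 68 / 0.90 = 75.6, rounded up to 76, or 152 in total.

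This agrees with the article, and nothing below changes it.

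**2. PAC count against time in AF.** Assumed: 25 PACs per hour in sinus rhythm, unchanged over time, and a full 24 h recording. PAC total = 25 × (24 − hours in AF).

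| Hours in AF | PAC total | Change from 600 | PACs per non-AF hour | AF burden |
|---|---|---|---|---|
| 0 | 600 | none | 25 | 0 min (0%) |
| 6 | 450 | −25% | 25 | 360 min (25%) |
| 12 | 300 | −50% | 25 | 720 min (50%) |
| 20 | 100 | −83% | 25 | 1200 min (83%) |
| 24 | 0 | −100% | undefined | 1440 min (100%) |

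The count falls in proportion to time in AF although the tendency to PACs is constant. Read upwards, the table shows recovery: a patient in continuous AF at baseline who regains sinus rhythm goes from 0 to 600. The rate per non-AF hour does not move, but it has no value in continuous AF, so AF status has to be read with it.

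**3. Effect on a group mean.** Assumed: patients in sinus rhythm average 600 PACs, and an extra fraction q of one arm is in continuous AF at month 3. The shift in that arm's mean is −600 × q:

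- q = 5%: −30
- q = 10%: −60
- q = 20%: −120

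Each shift appears as a benefit on the PAC count. The article does not say how many patients would be in AF, so these figures show only how the shift depends on q.

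**4. AF burden and the linear model.** If a share a of patients has any AF on the recording, a share 1 − a has a burden of exactly zero. For a = 10%, 25% and 50% (assumptions), 90%, 75% and 50% of the values are zero. A one-to-one transformation maps all zeros to one value, so the spike remains. The mean depends on a few patients: with 76 per group, one more patient in continuous AF moves the group mean by 1440 / 76 ≈ 19 minutes.

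**5. E/A.** No arithmetic applies. AF patients are eligible, E/A is listed without restriction to sinus rhythm, and the missing-data rule is general. Imputation under missing at random presumes a real value that was not observed. In AF there is none.

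**The case against.** **Progression to AF is already captured.** A reader might infer that the plan as a whole scores progression to AF as improvement. It does not. Any AF episode of at least 30 s fails the primary composite, AF burden rises with progression, and E/A becomes missing rather than better. In the 20-hour example the remaining 100 PACs still meet the threshold of 100, so that patient fails on both components. This objection stands in full and confines the problem to the PAC count read alone.

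**Recording time.** Undivided totals shrink with a short recording: 16 analysable hours of 24 would lower both by 1 − 16/24 = 33%. A reader might call this a bias. The article does not support that. The recording is nominally 24 h, one recorder model is used, the trial is double-blind, nothing indicates how often recordings fall short, and a minimum-wear rule may sit in the full protocol or SAP.

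**The word joining the two outcomes.** The Secondary outcome section links AF burden and PAC frequency as if they were alternatives. The Abstract and the Statistical analysis section list both separately, which settles that both are analysed.

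**Fallback methods and blinding.** The plan allows transformations or robust methods, and unblinding has two stages, so it would be wrong to say that raw values are the only option or that a method would be chosen on fully unblinded data. What remains is narrower. A transformation cannot remove the zeros, no robust method is named, and residuals are examined when the statisticians hold data split by group, although the group labels are still masked.

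**E/A imputation is inferred.** The article does not say that E/A will be imputed in AF patients; it states a general rule with no exception shown. E/A is one of six echocardiographic parameters, and only patients in AF at the echocardiogram are affected.

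**Conclusion.** The point holds for secondary outcomes and should be corrected; it does not threaten the primary analysis. The stated plan models PAC count alone in a population where AF is both an entry condition and a possible course, so that count falls with worsening into AF and rises with recovery. The illustrated size is an 83% apparent fall for 20 of 24 hours in AF, and a shift of 30 to 120 PACs in a group mean for 5% to 20% more patients in continuous AF. These rest on assumed PAC rates and AF shares that the article does not give; the direction needs only that PACs are not countable in AF. The zeros in AF burden need only that PAC-only patients are eligible, which they are. The E/A point depends on the general imputation rule being applied as written.

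**What to change.** 1. Express PACs per hour of analysable non-AF recording time, and AF burden as a percentage of analysable recording time.
2. Interpret PACs together with AF status. One way is a supportive ordered outcome in which any AF ranks worse than any PAC count, analysed by a proportional-odds model or a stratified rank test.
3. Name a rank-based or two-part method for AF burden now, in place of a linear model with an unnamed fallback.
4. Report E/A only for patients in sinus rhythm at the echocardiogram, and exclude it from imputation for patients in AF.

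The cost is analysis-plan wording and two derived variables from Holter files already being collected, with no added visits or participants. The small downside is that rank or two-part effects are less familiar to readers than a difference in means.

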#### Safety evaluation

Safety will be assessed through documentation of adverse events, physical examinations, vital signs, and laboratory tests, including complete blood count, electrolytes, liver function, and renal function. All laboratory results and reported adverse events will be used to evaluate the safety profile of WXKL. Any adverse event will be recorded promptly and in detail, noting the time of onset, duration, associated symptoms, relevant laboratory abnormalities, interventions taken, and outcome. These data will be reviewed to determine relatedness to WXKL. If a participant meets any predefined criteria for study discontinuation, the intervention will be stopped immediately, the treatment assignment will be unblinded as needed, and the participant will be managed to ensure a safe exit from the trial.

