
## Methods

### Study design and setting

This trial is a multicenter, double-blind, placebo-controlled study with two parallel groups designed to evaluate the efficacy of WXKL.The protocol was formulated in accordance with the SPIRIT statement and the Declaration of Helsinki (2013 Revision), as well as the Guidelines for Good Clinical Practice (GCP). The start and end of recruitment had been planned to be December 2025 and March 2028, respectively.

Before the experiment begins, researchers will conduct a training program to ensure that all participating medical staff fully understand each part of the trial. The trial will be conducted at multiple clinical centers in China, including Guang'anmen Hospital of the China Academy of Chinese Medical Sciences, Qilu Hospital of Shandong University, Xingtai People's Hospital, Affiliated Hospital of North China University of Science and Technology, Jinqiu Hospital of Liaoning Province, Tianjin Medical University Cancer Institute&Hospital, and Dezhou Second People's Hospital. After confirming eligibility and signing the informed consent form, 152 subjects receiving anthracycline treatment will be randomly allocated to either the WXKL or placebo groups in a 1:1 ratio. The study is divided into four phases: recruitment, allocation, intervention, and completion. Each participant will only be enrolled once. In addition to anthracycline chemotherapy and conventional anti-arrhythmic medications, participants will receive either WXKL or placebo treatment. During the study period, each participant will undergo three visits: baseline (Visit 1), month three (Visit 2), and month six (Visit 3). In Phase 1, participants are recruited from the oncology department, where they will undergo a physical examination and eligibility assessment. Those who match the inclusion criteria will receive a three-month pharmacological intervention. In Phase 2, following the completion of the intervention, participants will undergo clinical efficacy and safety assessments. Phase 3 is the follow-up period, during which participants will be followed up at the sixth month to gather their metrics again and assess clinical efficacy. The participant flowchart is shown in Figure 1, and the study schedule is shown in Table 1.

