### Intervention measures

Participants will be randomly assigned to either the intervention group or the control group and will receive treatment for 3 months. During the study period, the use of any other traditional Chinese medicines with similar components to WXKL will be prohibited. From Day 1 after enrollment, participants in the intervention group will receive WXKL (National Drug Approval Number Z10950026), while those in the control group will receive a matched placebo. Both treatments will be administered orally as granules dissolved in warm water, one sachet (5 g) three times daily. Drug dispensing will be managed by designated personnel, with careful counting and documentation to ensure accurate allocation according to the randomization code. At the end of the trial, all unused medications will be collected and destroyed by designated staff.

Concomitant medications: (a) All participants will receive anthracycline-based chemotherapy according to standardized regimens prescribed by their treating physicians (24, 25). (b) According to current clinical guidelines, *β*-blockers are recommended as first-line agents for ventricular rate control in atrial arrhythmias. Therefore, for patients with symptoms or clinical indications, *β*-blockers will be administered as background antiarrhythmic therapy. The initiation, dose titration, and anticoagulation strategies will be determined based on patients' clinical status and relevant guidelines (26), to ensure both safety and consistency across study centers. (c) Concomitant use of medications for other comorbid conditions will be permitted. However, the use of other anti-arrhythmic drugs (except *β*-blockers) will be prohibited to minimize potential confounding effects. In addition, the use of cardio-protective agents specifically targeting anthracycline-induced cardiotoxicity, such as dexrazoxane, will not be allowed. All concomitant medications during the study will be recorded in detail in the case report forms (CRF).

Assigned interventions may be discontinued or modified in cases of serious adverse events, participant withdrawal, or clinical deterioration. Any such changes will be fully documented and submitted to the ethics committee for review.

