### Data security monitoring and management

The study team provided coordination and daily support for the trial. The study leader, [name], supervised the study design and provided guidance throughout trial implementation. Study leader was responsible for all aspects of local organization, including identifying potential recruits and taking consensus. The trial steering committee is composed of the study leader ([name]), the site principal investigators ofrom each participating center, and co-investigators. Questions that arise during the research process will be submitted to the committee for decision-making. Finally, clinical research associates (CRAs) will supervise the study progress at any time and hold a meeting monthly. Prior to trial initiation, an independent Data Monitoring Committee (DMC) is convened, comprising five experts from the fields of oncology, cardiology, biostatistics, clinical trial methodology, and bioethics. This committee is responsible for safety monitoring, reviewing, and evaluating detailed information on adverse events across groups. Based on its assessments, the DMC may recommend early trial termination, suggest measures to mitigate risks, or advise adjustments to the study plan.

For every participant, whether completing the study or withdrawing, the CRF should be carefully completed in accordance with the study protocol after completing the Case Screening Form. The principal investigator at each site is responsible for the authenticity of the data collected at their center. Data management is uniformly conducted using the electronic data capture (EDC). Specifically, after a participant's visit, the investigator will enter data from the paper CRF into the EDC system. Following submission, the data will be reviewed by a monitor before being transferred to the data management company. If any queries arise regarding the CRF, the data manager will generate a Data Resolution Query (DRQ). This query will be sent to the investigator via the clinical monitor. The investigator is expected to respond promptly. The data manager will then update the database based on the investigator's response, issuing further DRQ if necessary. After blinded review and confirmation of the database's accuracy, the principal investigator and statistical analyst will lock the data. Once locked, the data files will no longer be modified, and the raw data will be retained for at least five years following the study's conclusion.

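### The safety section does not separate stopping study medication from leaving the trial, so a participant stopped for safety before month 3 may have no month-3 Holter

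*Protocol article*

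**What the plan says.** All references are to the protocol article.

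- **Safety evaluation:** "If a participant meets any predefined criteria for study discontinuation, the intervention will be stopped immediately". The same sentence provides for unblinding as needed and ends: "the participant will be managed to ensure a safe exit from the trial". It mentions no later visit.
- **Intervention measures:** "Assigned interventions may be discontinued or modified in cases of serious adverse events, participant withdrawal, or clinical deterioration". This provision concerns the drug. It does not say whether the participant then stays or leaves.
- **Measurements:** of the endpoint assessors, "They conduct regular data collection and follow-up for all participants according to the study protocol schedule", with time points at months 3 and 6.
- **Study design and setting, and Table 1:** three visits only (baseline, month 3, month 6), each with a 24 h Holter.
- **Statistical analysis:** the primary analysis is by intention to treat, "including all randomized participants and analyzing them according to their assigned groups". "Missing data will be handled using multiple imputation under the assumption of missing at random, and sensitivity analyses will be performed".
- **Data security monitoring and management:** "For every participant, whether completing the study or withdrawing, the CRF should be carefully completed" under the protocol. No Holter is named there.
- **Sample size calculation:** 29% versus 10% free of atrial arrhythmia, 68 per group, raised to 76 per group for 10% dropout.

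**The concern.** The safety sentence attaches three consequences to one trigger: the drug stops, the blind may be broken, and the participant leaves. A safety stop is a reason to stop the drug. It is not in itself a reason to stop observing the participant.

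The primary outcome rests on one 24 h recording at month 3, and nothing is scheduled between baseline and that visit. If the sentence is followed as written, a participant stopped for safety in the first three months contributes no outcome and is imputed under missing at random. People who stop because of harm or deterioration are those for whom that assumption is weakest. The planned sensitivity analyses can show how far the result depends on it, but they cannot recover a recording that was never made. Adverse events that begin after the exit may also be lost, in a trial that sets out to describe the safety of WXKL in patients on chemotherapy.

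**Working it through.** **1. The plan's own figure.** Inputs from Sample size calculation: 29% versus 10%, two-sided 5%, 80% power. Pooled two-proportion formula without continuity correction, with mean rate 0.195:

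n = [1.960 × √(2 × 0.195 × 0.805) + 0.842 × √(0.29 × 0.71 + 0.10 × 0.90)]² / 0.19² = 67.1, so 68 per group. Then 68 / 0.90 = 75.6, so 76 per group and 152 in total. The stated figures reproduce, and nothing below changes them.

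**2. The text side by side.**

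| Section | Trigger | Drug | Participant |
|---|---|---|---|
| Safety evaluation | predefined study-discontinuation criterion | stopped | leaves the trial |
| Intervention measures | serious adverse event, withdrawal, clinical deterioration | stopped or modified | not stated |
| Measurements | none (everyone) | not stated | followed at months 3 and 6 |

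The first two rows have different triggers, and the second is silent on exit, so they do not contradict each other. The gap is that no row says what happens to the visits of someone whose drug is stopped for safety, while the first row points to exit.

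**3. Illustrative size of the bias.** The article gives neither the number of exits nor their success rate, so both are assumed here. Let k participants of 76 in an arm leave before month 3 with true success rate s, and let imputation assign them their arm's planned rate p.

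True arm rate = [(76 − k) × p + k × s] / 76. Error in the arm rate = k × (p − s) / 76.

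| Exits | True success s | True rates, WXKL vs placebo | True difference (assumed 19) | True RR (assumed 2.9) |
|---|---|---|---|---|
| 2 WXKL | 10% | 28.5% vs 10% | 18.5 | 2.85 |
| 4 WXKL | 10% | 28.0% vs 10% | 18.0 | 2.8 |
| 8 WXKL | 10% | 27.0% vs 10% | 17.0 | 2.7 |
| 8 WXKL | 0% | 25.95% vs 10% | 15.95 | 2.59 |
| 8 WXKL | 29% | 29.0% vs 10% | 19.0 | 2.9 |
| 8 WXKL | 48% | 31.0% vs 10% | 21.0 | 3.1 |
| 8 placebo | 0% | 29% vs 8.95% | 20.05 | 3.24 |
| 8 placebo | 29% | 29% vs 12.0% | 17.0 | 2.42 |
| 8 in each arm | 0% | 25.95% vs 8.95% | 17.0 | 2.9 |

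Eight per arm is the whole dropout allowance (76 − 68 = 8), so these rows are an upper illustration. The error runs in both directions and vanishes when the imputed rate is right.

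**4. Power cost of measuring off-drug participants.** Pooled z-test, two-sided 5%, with exits succeeding at 10%:

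| Exits | Outcomes measured | Outcomes lost |
|---|---|---|
| 8 per arm | 27% vs 10%, 76/76: 77.6% | 29% vs 10%, 68/68: 80.5% |
| 8 WXKL only | 27% vs 10%, 76/76: 77.6% | 29% vs 10%, 68/76: 82.9% |
| 4 WXKL only | 28% vs 10%, 76/76: 81.4% | 29% vs 10%, 72/76: 83.9% |

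The higher figures in the last column are for an effect that leaves the exits out.

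**The case against.** The strongest reply is that the trigger is study discontinuation, not drug discontinuation. On the plain words the article already has one provision for stopping the drug and another for leaving the study, and leaving after meeting a criterion for leaving is no error. The criteria themselves belong in the full protocol and are not missing from an article. If they cover only withdrawal of consent, exit is correct and the rewording changes little. This stands, and it limits the point. It does not remove it: the sentence sits in the safety section and comes with immediate stopping and unblinding, which suggests that safety stops are also meant.

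The sentence also does not expressly cancel later visits or rule out an exit assessment, and the case report form is to be completed for those who withdraw. That shows early leavers were considered, but no Holter is called for. Each adverse event's duration and outcome must be recorded, which covers much of what is needed for events already open at the stop. It does not cover events that start later.

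Two stronger readings are tempting, and the article supports neither:

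- **That Intervention measures contradicts the safety section** by stopping the drug while keeping the participant in the trial. It says nothing about staying or leaving, and one of its listed reasons is withdrawal.
- **That the exit rule breaches intention-to-treat or the planned follow-up of everyone.** Participants who leave stay in the analysis set through multiple imputation, and 10% dropout is allowed for. That allowance protects power. It does not protect against bias.

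**Conclusion.** The point holds in a limited form. The safety sentence merges stopping medication with leaving the study, and followed as written it produces avoidable missing primary outcomes where missing at random is least credible. This weakens the intention-to-treat analysis and the follow-up of all participants without breaching either.

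The conclusion rests on the inference that the unlisted criteria include safety stops. The size of the bias is unknown and probably small, and its direction is uncertain. Under the assumed scenarios, 2 to 4 WXKL exits at 10% success move the 19-point effect by 0.5 to 1.0 points, and using the whole dropout allowance in one arm moves it by at most about 3 points. A reader might infer from the rows with 8 exits that the trial would be biased in favour of WXKL. The article does not support that, because it gives no exit count or success rate and other equally assumed values reverse the sign. No stated figure changes. Severity: minor; a cheap improvement.

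**What to change.** Reword the sentence in Safety evaluation so that meeting a criterion stops study medication only. Suggested text: study medication is discontinued and the assignment unblinded if clinically needed; unless the participant withdraws consent for follow-up, Visits 2 and 3, including the 24 h Holter, echocardiography, laboratory tests and adverse events, take place on the original calendar from enrollment; adverse events open at stopping are followed until resolved or stable. Reserve exit from the trial for withdrawal of consent for follow-up.

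The cost is one reworded passage, site training, and some effort to bring back participants who are off the drug. No visit is added, because Visits 2 and 3 are already scheduled for everyone, and the sample size stays at 152. Measured off-drug outcomes may dilute the effect slightly: with 8 exits per arm at 10% success, power is about 78% rather than about 81%. The gain is less missing data and less room for bias. It does not guarantee an unbiased estimate, since participants who withdraw consent or cannot attend will still leave gaps. The change helps only participants whose visits are still to come, so it should be made promptly.
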